## Abstract

**Background:**

Over 65% of stroke survivors are either overweight or obese and have multiple cardiovascular risk factors. However, few studies have examined the effects of comprehensive lifestyle behavior interventions to promote weight loss and control cardiovascular risk factors in stroke survivors. Thus, the purpose of this study is to examine a novel behavior change approach - SystemCHANGE™ - to promote weight loss and improve health and function in stroke survivors. SystemCHANGE™ focuses on redesigning the social environment to achieve a specific goal.

**Methods:**

We will conduct a randomized controlled pilot study to examine the efficacy, feasibility, and safety of the SystemCHANGE™ weight management program in overweight and obese stroke survivors. The central hypothesis of the study is that the SystemCHANGE™ intervention will help overweight and obese stroke survivors lose 5% of their body weight, thereby improving health and function. Thirty-five stroke survivors will be randomized into either the 6-month SystemCHANGE™ intervention or a contact-control intervention. Outcome measures will be assessed at baseline and again at 3 and 6 months after the interventions. Body composition will be assessed using a Bod Pod. Patient-reported outcomes will be the Stroke Impact Scale and Reintegration to Normal Living Index. Objective outcomes will include the 6-Minute Walking Test and Rivermead Motor Assessment.

**Discussion:**

This study will be the first randomized controlled trial to evaluate the efficacy and safety of a weight management intervention in stroke survivors using the SystemCHANGE™ approach. Furthermore, it will be the first empirically-examined comprehensive lifestyle intervention designed to target physical activity, nutrition, and sleep to promote weight loss in stroke survivors.

**Trial registration:**

ClinicalTrials.gov Identifier: NCT01776034

## Background

Over 65% of stroke survivors are either overweight or obese, and a projected 4.98 million stroke survivors in the USA have multiple cardiovascular risk factors [1]. Stroke survivors are at significant risk for de-conditioning [2], elevated inflammatory markers [3], and insulin resistance [4], which subsequently increases risk for secondary stroke and cardiovascular disease [5,6]. Engaging in healthy behaviors, such as physical activity, good sleep hygiene, and nutrition, to facilitate energy balance may help reduce the risk of secondary conditions and ultimately improve physical function and quality of life in stroke survivors [5,7].

However, stroke survivors can experience many barriers to engaging in a healthy lifestyle to achieve energy balance [8]. Mental and physical impairments interacting with a non-supportive environment can create multiple challenges to engagement in healthy behaviors, which can perpetuate a disabling cycle [9]. Specifically, inactivity, unhealthy eating, and poor sleeping habits can lead to obesity. Obesity can increase mobility problems, fatigue, depression, and further difficulties engaging in healthy behavior. Supporting stroke survivors to achieve energy balance and a healthy body weight may be a strategy to counteract the disablement process.

Most studies examining lifestyle interventions in stroke survivors have focused on promoting physical activity and/or teaching self-management skills [10], which only partially addresses behaviors associated with achieving energy balance [11]. Thus, effective strategies to promote weight loss in stroke survivors remain elusive. Research in the general population indicates weight management interventions should target both physical activity and nutrition [11], and that promoting good sleep hygiene may be an additional strategy to facilitate weight loss [12]. Furthermore, research in people with disabling conditions indicates that impairments often create barriers to engagement in healthy behaviors, but that utilizing self-management skills and having ample social support can facilitate overcoming such health-related barriers [13]. Thus, based on research in the general population and in people with disabling conditions, we contend that an effective weight management intervention in stroke survivors should target physical activity, nutrition, sleep, and self-management skills, as well as utilize strategies to foster a supportive social environment.

[name] recently developed such an intervention approach called SystemCHANGE™ [14], a new behavior change intervention drawing from social ecological theories [15-17]. SystemCHANGE™ focuses on redesigning the environment using trial-and-error ‘experiments’ to achieve a specific goal. SystemCHANGE™ is in contrast to cognitive-behavioral interventions that focus on changing a person’s viewpoint of a situation and increasing motivation. In SystemCHANGE™_,_ individuals are taught a set of skills to assist them in incorporating habitual lifestyle behaviors into their daily systems so they succeed despite wavering motivation. Strategies include identifying a chain of steps/events that comprise the system in which the desired change is to occur, keeping track of data about the system process to understand it, implementing short trials of possible improvement solutions, evaluating success by reviewing data, and making provisions for holding the gains. Given the novelty of SystemCHANGE™ to focus on an individual’s surrounding environment rather than an individual’s motivation and willpower to change behavior, this approach is now being tested in various population segments (for example, overweight children and patients with HIV). We propose to adapt the SystemCHANGE™ intervention approach to promote weight loss in overweight and obese stroke survivors. This study will represent the first empirically-examined comprehensive lifestyle intervention designed to target physical activity, nutrition, and sleep to promote weight loss in stroke survivors.

The specific aims are to engage stroke survivors and their families as co-designers to adapt the SystemCHANGE™ intervention, and then conduct a randomized controlled pilot study to provide preliminary estimates of the intervention’s efficacy in 35 stroke survivors. Herein, we will focus on describing the methodology for the pilot randomized controlled trial rather than the qualitative methodology. The pilot study will provide effect size estimates on the following primary outcomes: body weight and patient-reported and objective outcomes of health and function. Secondary outcomes include questionnaires on symptoms, healthy behaviors, psychosocial mediators, and biomarkers of cardiovascular risk. The central hypothesis of the study is that the SystemCHANGE™ intervention will help overweight and obese stroke survivors lose 5% of their weight, thereby improving health and function. Hypothesized mechanisms of action will involve significant improvements in healthy behaviors, symptoms, psychosocial constructs, and cardiovascular risk.

## Methods

### Trial design

We will conduct a single-center, randomized, controlled, parallel-group, rater-blinded pilot study. Thirty-five participants will be recruited and randomized into the SystemCHANGE™ intervention or a contact-control information-only intervention. Both interventions will be delivered over a 6-month period. All outcomes will be administered before the interventions and again at 3 and 6 months. The Cleveland Clinic Institutional Review Board approved this study. We will obtain informed consent from each stroke survivor that participates in the study.

### Participants

The following methods will be used for recruitment: (1) fliers distributed at support groups; (2) referrals from clinicians; and (3) medical chart reviews. Individuals will undergo a three-part screening to confirm eligibility (phone, physician, and in-person). Subjects who meet the eligibility requirements over the phone will be mailed a demographic sheet and a release form to contact their physician. Once we confirm eligibility from their physician, arrangements will be made to re-confirm eligibility in person, obtain informed consent, collect pre-test data, and randomize participants into the SystemCHANGE™ intervention or the control intervention. Main inclusion criteria are: (1) a physician-confirmed unilateral ischemic or hemorrhagic stroke (at least 6 weeks post-stroke); (2) physician consent to participate; (3) age 30 to 75 years; (4) a BMI between 25 to 40 kg/m^2^; and (5) a stable weight for the past 4 weeks. Individuals will be excluded if they have: (1) heart disease (that is, myocardial infarction, congestive heart failure, coronary artery bypass grafting, or valve replacement during the past 3 months, serious cardiac arrhythmias, hypertrophic cardiomyopathy, and severe aortic stenosis); (2) pulmonary embolus; (3) uncontrolled resting blood pressure (that is, 140/90 mmHg) or abnormal blood pressure or heart rate response during the 6-Minute Walking Test [18] (for example, drop in systolic blood pressure of >10 mmHg from baseline), (4) uncontrolled diabetes (hospitalized in the past 6 months); (5) unable to communicate (for example, severe aphasia); (6) severe cognitive deficits (weighted score <12 on the short version of the Blessed Orientation Memory Concentration test [19]); (7) pregnancy; (8) three or more falls in the past month; (9) inability to walk 3 meters with or without a mobility device; (10) weight loss medications or medications that cause excessive weight gain (for example, corticosteroids and antipsychotic); and (11) gastric bypass surgery.

Study criteria were selected to help ensure patient safety, create a homogeneous sample of mild to moderate impairments, minimize confounders, and avoid ceiling effects. We are excluding individuals >75 years of age to minimize risk of weight loss, muscle atrophy, and functional declines. Individuals with serious heart conditions are being excluded because of the prescription of a physical activity program. We are also excluding people with uncontrolled blood pressure or diabetes because these individuals need medical treatment, which will likely result in prescribing or changing medications that can confound study results.

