### Sample size

Our goal to recruit 35 stroke survivors is consistent with recommendations in the literature for pilot studies. Hertzog [32] has shown that samples of 10 to 20 participants per group are often adequate for evaluating feasibility in a pilot study. Furthermore, Dobkin [33] has suggested that 15 participants in each research arm are sufficient for determining whether a larger multicenter trial should be conducted.

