### Randomized allocation procedure

Allocation will be performed using a permuted block randomization procedure to help ensure a 1:1 ratio in each group. The allocation sequence will be determined using a computerized random number generator with block sizes of four participants. The allocation sequence will be concealed from the health education specialist and researchers who are enrolling potential participants with a sequential number of opaque sealed envelopes. Envelopes will be opened only after all pre-test data is collected. A researcher with no involvement in the delivery of the interventions or the screening of participants will prepare the envelopes.

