### Statistical methods

Recruitment and data collection efforts will be managed with Research Electronic Data Capture [34]. The first step in the analysis will be to compute summary statistics, calculate outcome scores, and conduct quality control assessments. Outcome measures will be analyzed using multivariate repeated measures or one-way ANOVAs (assuming data are normally distributed). Between-subject effects will be examined by subtracting baseline scores from post-test scores and utilizing one-way MANOVA to determine whether there are significant improvements in change scores in the SystemCHANGE™ group compared to the contract-control group. Within-subject effects will be examine with repeated-measures MANOVA comparing baseline data immediately before the SystemCHANGE™ intervention to data at 3 and 6 months after receiving the SystemCHANGE™ intervention. To help minimize missing data, we will follow recommendations by Little *et al*. [35] (for example, providing monetary incentives). Effect sizes will be calculated as Cohen’s d. Feasibility and safety of the intervention will be assessed with descriptive statistics (frequencies, percentages, means, and standard deviations): number of contacted *versus* recruited subjects, reasons for non-participation, attrition (with timing and reasons), time required to train health education specialist and arrange follow-up phone calls, and adverse event monitoring (control *versus* treatment group).

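### Entry is open-ended from 6 weeks post-stroke, but the function analyses ignore time since stroke: this costs precision between arms and biases the SystemCHANGE-only pre/post test upward

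*Protocol article*

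**What the plan says.** **Entry.** Participants lists, among the main inclusion criteria, "unilateral ischemic or hemorrhagic stroke (at least 6 weeks post-stroke". No maximum time since stroke is given. The same section says the criteria were chosen to "create a homogeneous sample of mild to moderate impairments, minimize confounders, and avoid ceiling effects".

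**Size and allocation.** Trial design: "Thirty-five participants will be recruited and randomized into the SystemCHANGE™ intervention or a contact-control information-only intervention". Randomized allocation procedure: "Allocation will be performed using a permuted block randomization procedure to help ensure a 1:1 ratio in each group", using a "computerized random number generator with block sizes of four participants". No stratification factor is named.

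**Outcomes.** The end of Background places patient-reported and objective health and function, with body weight, among the primary outcomes for which the pilot is to estimate effect sizes. Outcomes names the Stroke Impact Scale, Reintegration to Normal Living Index, 6-Minute Walking Test and Rivermead Motor Assessment.

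**Analysis.** Statistical methods fixes two analyses. For the comparison with control: "Between-subject effects will be examined by subtracting baseline scores from post-test scores and utilizing one-way MANOVA". For change inside one arm: "Within-subject effects will be examine with repeated-measures MANOVA comparing baseline data immediately before the" SystemCHANGE intervention with the 3- and 6-month data. Neither includes a covariate.

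**Confounders.** Potential limitations and confounders lists medication changes, the multi-component intervention and non-responders. Time since stroke is not listed.

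**The concern.** A person who enters at week 6 is followed to about week 32 after the stroke (6 + 26). Another may enter years later, when little spontaneous change is expected. If early entrants improve on walking, motor function and participation regardless of arm, that improvement is part of their change score. Subtracting baseline does not remove it, because recovery is itself change from baseline.

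Two different things are at stake. Between arms, the early/late mixture adds variance to the effect-size estimates that the pilot exists to supply, and a chance surplus of early entrants in one arm goes uncorrected. Within the SystemCHANGE arm there is no comparator, so all spontaneous recovery reads as response to the intervention.

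**Working it through.** **The plan's own figure.** The sample size of 35 comes from pilot rules of thumb ("samples of 10 to 20 participants per group are often adequate for evaluating feasibility in a pilot study", and 15 per arm). No alpha, power, effect size, SD or dropout is stated, so there is no formula to reproduce. It is consistent with the rules: 35/2 = 17.5 per arm lies within 10 to 20, and 30 completers would leave 5/35 = 14% for attrition.

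**Inputs.** From the article: N = 35 at 1:1, taken as 18 and 17; change-score analysis; no covariate. Assumed, because the documents do not give them: q, the share of early entrants, and g, their extra spontaneous gain in units of the change-score SD among people with the same time since stroke. The main case is q = 0.3 with g = 0.25, 0.5 and 1.0.

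**1. Variance between arms.** The mixture adds q(1−q)g² to a residual variance of 1. Its share of the total is q(1−q)g² / (1 + q(1−q)g²). Removing it is worth 1/(1 − share) − 1 = q(1−q)g² more participants, before the small loss of degrees of freedom. With q(1−q) = 0.21:

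| g | 0.21 × g² | share of variance | equivalent extra participants |
|---|---|---|---|
| 0.25 | 0.013 | 1.3% | 1.3% |
| 0.5 | 0.053 | 5.0% | 5.3% |
| 1.0 | 0.210 | 17.4% | 21% |

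Over q = 0.2 to 0.5 and the same g, the SD is inflated by 0.5% to 12%, and the share of variance runs from 1% to 20%.

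**2. Chance imbalance.** With K early entrants among 35, the number falling in the arm of 18 is hypergeometric if time since stroke plays no part in allocation.

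| early entrants K | P(gap ≥ 20 points) | P(gap ≥ 30 points) |
|---|---|---|
| 7 | 9% | 1% |
| 10 | 26% | 6% |
| 14 | 31% | 9% |
| 18 | 18% | 9% |

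(The figures do not rise steadily because only certain gaps are possible.) Simulating blocks of four gives nearly the same values, about 0.26 for 10 early and 0.30 for 14, so blocking does not balance this factor. A 20-point gap shifts the contrast by 0.2 × g = 0.05 to 0.20 SD.

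**3. Steps 1 and 2 are one effect.** The standard error of a standardised difference is √(1/17 + 1/18) = 0.338. With 10 early, the SD of the gap between arms is 0.155, so at g = 1.0 imbalance adds a component with SD 0.155: √(0.338² + 0.155²) = 0.372. Inflating the residual SD gives the same figure: 0.338 × √1.21 = 0.372. The two must not be added together.

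**4. Within-arm test.** With no comparator, the extra recovery of early entrants raises the mean change in the SystemCHANGE arm by q × g. At q = 0.3 this is 0.3 × 0.25 = 0.075, 0.3 × 0.5 = 0.15 and 0.3 × 1.0 = 0.30 SD. Over q = 0.2 to 0.5 it runs from 0.05 to 0.50 SD. A larger sample would not reduce it.

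**The case against.** **The control arm already handles recovery.** Allocation is randomised and concealed, so both arms draw on the same distribution of time since stroke and spontaneous recovery cancels in expectation. This stands. A reader might infer that the between-arm comparison is confounded with recovery; the documents do not support that. What remains is chance imbalance, which the wider unadjusted standard error already reflects.

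**The size is assumed.** Neither q nor g is in the article. A reader might push g to 1.5 SD and quote a 47% gain (0.21 × 2.25 = 0.47), but nothing in the documents points there. At 0.25 to 0.5 SD the gain is only 1% to 5%, small beside a standard error of 0.34 SD. This also stands.

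**Covariates belong in the analysis plan.** This would answer the point if the article were silent. It is not: it names a one-way model of change scores, and the point is about that stated choice. The intention, under limitations, to explore patient characteristics names no variable and concerns who responds, not adjustment.

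**The homogeneity aim refers to impairment.** This is fair. The open entry window sits awkwardly with that aim but does not contradict it, and no contradiction is claimed.

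**The within-arm weakness is generic.** Any single-arm pre/post test is uncontrolled, and the article does not say that this one establishes efficacy. Both are true. Even so, open entry from 6 weeks gives the bias a specific source and direction for function outcomes, and the article plans the test alongside the controlled comparison without limiting how it will be read.

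**Conclusion.** The point holds in two parts of unequal strength.

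- **Within arm:** a systematic upward bias for the function outcomes if the pre/post change is read as intervention effect, of about 0.08 to 0.30 SD at 30% early entrants and 0.25 to 1.0 SD extra recovery.
- **Between arms:** no bias in expectation, but avoidable loss of precision and unadjusted chance imbalance, worth about 1% to 21% more participants under the same assumptions and near the lower end if extra recovery is 0.5 SD or less.

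Both rest on the assumption that early entrants gain more spontaneously over six months than late entrants. If the sample turns out to contain few early entrants, both shrink towards zero. The point concerns the function outcomes; it is not made for the 5% weight-loss hypothesis. It does not show that the randomised comparison is invalid, or that 35 people must be stratified by time since stroke. It is a worthwhile improvement to a stated analysis, not a fatal flaw.

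**What to change.** In Statistical methods:

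1. Analyse each function outcome between arms by ANCOVA or a mixed model, with the outcome's own baseline value and time since stroke at randomisation (for example log weeks) as pre-specified covariates.
2. Report the SystemCHANGE-only pre/post comparison as descriptive, and state that it is not evidence of effect on function.

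**Cost.** Two covariates take about two degrees of freedom out of about 33 (35 − 2), leaving about 31. The outcome's own baseline differs by outcome, so separate models replace the one-way MANOVA; this is a change of method and not only of wording. Time since stroke has to be known to apply the 6-week rule, but a yes/no check could satisfy that rule, so the plan should say that the actual interval is recorded. Eligibility and allocation need not change.

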### Interventions

#### SystemCHANGE™

The SystemCHANGE™ intervention will be delivered over a 6-month period involving 12 face-to-face group sessions (1.5 h each) held weekly for 3 months, followed by 3-monthly ‘booster calls’. Intervention groups include up to 10 patients, and family is encouraged to attend. Intervention sessions consist of 30-min of behavior change activities and 60-min focused on healthy behaviors. Sessions will be led by a health education specialist and held at local community centers. Below we outline each topic area of the SystemCHANGE™ intervention.

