#### Contact-control intervention

In contrast to the SystemCHANGE™ arm, participants assigned to the information-only group will receive pamphlets that contain information on healthy eating, physical activity, sleep, and symptom management, and will be telephoned at the same time points as the SystemCHANGE™ sessions. These 20-min phone calls are intended to teach participants recommended guidelines for engaging in healthy behaviors and reducing cardiovascular risk. However, the skills taught in the SystemCHANGE™ intervention (for example, identifying a chain of steps/events that comprise the system in which the desired change is to occur) will not be taught in the control intervention. Thus, we will be able to determine whether it is the skills taught in the SystemCHANGE™ intervention or simply the learning of guidelines that promotes engagement in healthy behaviors. Furthermore, the phone calls in the contact-control intervention will provide an equivalent number of contacts with the health education specialist as in the SystemCHANGE™ intervention. Thus, we will be able to determine whether it is the skills taught in the SystemCHANGE™ intervention or simply the interactions with the health education specialist and creating accountability that promotes engagement in healthy behaviors.

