#### Treatment fidelity

To promote standard application of the interventions in both the SystemCHANGE™ group and the control group, a manual of operating procedures and lesson plans outlining each session will be provided to the health education specialist and incorporated into their training. We will use the same person to deliver the interventions in both groups to facilitate standardized delivery. The health education specialist will also be given a checklist to review and use in each session and will be monitored in-person at random intervals to determine the extent to which the lesson plans are followed. Intervention fidelity will be further monitored by tracking participant attendance, monitoring completion of homework assignments, and administering quizzes to assess participants’ understanding of the material.

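### SystemCHANGE is delivered in shared groups but analysed as if all participants were independent; if outcomes correlate within groups, standard errors are too small

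*Protocol article*

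**What the plan says.** **SystemCHANGE arm.** The section SystemCHANGE™ describes "12 face-to-face group sessions (1.5 h each) held weekly for 3 months", and adds: "Intervention groups include up to 10 patients, and family is encouraged to attend". Booster calls follow in the second three months.

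**Control arm.** Under Contact-control intervention, participants get pamphlets and "will be telephoned at the same time points as the SystemCHANGE™ sessions". The calls last 20 minutes, and no group contact is described.

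**Deliverer.** Under Treatment fidelity: "We will use the same person to deliver the interventions in both groups to facilitate standardized delivery".

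**Allocation and size.** Individuals are randomized 1:1 in blocks of four. On size: "Our goal to recruit 35 stroke survivors is consistent with recommendations in the literature for pilot studies". The support offered is rules of thumb, for example that "samples of 10 to 20 participants per group are often adequate for evaluating feasibility in a pilot study".

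**Analysis.** Statistical methods states: "Outcome measures will be analyzed using multivariate repeated measures or one-way ANOVAs (assuming data are normally distributed"). It then specifies a one-way MANOVA on change scores between arms and a repeated-measures MANOVA within the SystemCHANGE arm, with effect sizes as Cohen's d. Normality is the only model assumption named. Session group does not appear in the sample size, the analysis or the listed limitations.

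**The concern.** The design is partially nested: one arm is clustered in session groups and the other is not. In a one-way model, arm is the only factor and every participant counts as an independent observation. Members of one SystemCHANGE group share 12 sessions of 1.5 hours (18 hours), the same discussions and the same peers, so some positive correlation in their outcomes is plausible.

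If it exists, the variance of the SystemCHANGE mean is understated. The between-arm tests then reject too often, and the effect sizes look more precise than they are. The within-arm tests are more exposed, because every participant in them belongs to a group. Since the Discussion says the pilot is meant to supply effect sizes for a larger trial, overstated precision and a missing design effect could carry over into that trial's planning.

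This concerns a model that the article names. It is not a detail left to an analysis plan.

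**Working it through.** **Stated figure.** The total of 35 comes from no formula, so there is no calculation to reproduce. It gives 35/2 = 17.5 per arm, which lies within 10 to 20 per group and above 15 per arm, as the cited rules require.

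**Inputs from the article.** N = 35 allocated 1:1, so 17 or 18 per arm; groups of up to 10 in the SystemCHANGE arm, so at least two groups; no groups in the control arm.

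**Assumptions.** ICC of 0.01 to 0.10; 18 SystemCHANGE participants (n_T) and 17 controls (n_C); two groups of 9, three of 6, or four of 5, 5, 4 and 4; equal total variance in both arms; two-sided 5% level.

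**Formulas.**
- Mean cluster size m = Σm_j²/Σm_j. For four groups this is (25 + 25 + 16 + 16)/18 = 4.56.
- Design effect in the SystemCHANGE arm: DE = 1 + (m − 1) × ICC.
- True SE over independence SE, between arms: √[(DE/n_T + 1/n_C)/(1/n_T + 1/n_C)].

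**Example, two groups of 9, ICC 0.10.** DE = 1 + 8 × 0.10 = 1.80. The effective size of the arm is 18/1.80 = 10.0. The SE ratio is √[(0.1000 + 0.0588)/(0.0556 + 0.0588)] = √1.389 = 1.18.

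| Layout | ICC | DE | Effective n | SE ratio | Type I error |
|---|---|---|---|---|---|
| 2 × 9 | 0.01 | 1.08 | 16.7 | 1.02 | 5.5% |
| 2 × 9 | 0.05 | 1.40 | 12.9 | 1.09 | 7.3% |
| 2 × 9 | 0.10 | 1.80 | 10.0 | 1.18 | 9.7% |
| 3 × 6 | 0.01 | 1.05 | 17.1 | 1.01 | 5.2% |
| 3 × 6 | 0.05 | 1.25 | 14.4 | 1.06 | 6.4% |
| 3 × 6 | 0.10 | 1.50 | 12.0 | 1.12 | 8.0% |
| 5, 5, 4, 4 | 0.01 | 1.04 | 17.4 | 1.01 | 5.2% |
| 5, 5, 4, 4 | 0.05 | 1.18 | 15.3 | 1.04 | 6.0% |
| 5, 5, 4, 4 | 0.10 | 1.36 | 13.3 | 1.08 | 7.1% |

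Type I error is simulated for the two-sample t test on change scores under no effect, the univariate form of the one-way analysis. Runs of 100,000 agree within about 0.3 percentage points. At ICC 0 the rate is 5.0%.

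**Within the SystemCHANGE arm.** The SE ratio is √DE, which for two groups of 9 is √1.08 = 1.04 to √1.80 = 1.34. A one-sample t test on change then has type I error of about 5.9% to 14.4%. This only indicates the scale, because the planned test is a repeated-measures MANOVA.

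**Cost of a partially nested mixed model.** The SystemCHANGE mean would be judged on (groups − 1) degrees of freedom. The Satterthwaite formula is df = (a + b)²/[a²/(k − 1) + b²/(n_C − 1)], with a = DE/n_T, b = 1/n_C and k groups. At expected variances, two groups of 9 give 3.7, 3.0 and 2.5 df at ICC 0.01, 0.05 and 0.10, and intervals 1.44, 1.72 and 2.09 times as wide as under independence. Three groups of 6 give about 7 df at ICC 0.01, falling to 5.5 at 0.10, and intervals 1.17 to 1.37 times as wide.

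**The case against.** The strongest case against is that the harm is conditional and may be small.

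- **No ICC or number of groups is given.** At ICC 0 there is no error, and at 0.01 it is negligible. Two groups of 9 is close to the worst layout the text allows. This stands, and is why the result is stated as a range.
- **Features that could weaken the correlation.** Diet plans are personalized, activity follows the patient's preference, and group sessions end at month 3, so the 6-month outcome comes three months later. The support described is mainly family and caregivers, not group peers. This bears on size. Having one specialist in both arms removes differences between deliverers, but not correlation within session groups.
- **It is a pilot.** No power, significance level or progression threshold is stated, and ignoring clustering does not materially shift the point estimate of Cohen's d. This stands and lowers the severity. The section does plan significance tests, however, and effect sizes are a main product.
- **A condensed article may leave clustering to a fuller plan.** That would excuse missing detail. It does not cover the choice of a one-way model, which the article states.
- **The calculations are univariate.** This stands. They show the scale of the problem, not the exact error of the MANOVA.

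A reader might infer that the standard errors are certainly too small, or that 35 participants is invalid. The documents support neither: the first needs a positive ICC that they do not give, and the second fails because the sample size makes no power claim. Individual control calls are also an inference, from the description of telephone contact.

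**Conclusion.** The mismatch between design and model holds: group delivery in one arm only, and a stated analysis that assumes independence. Its consequence is conditional on positive within-group correlation. Over an assumed ICC of 0.01 to 0.10, the true between-arm SE is 1.02 to 1.18 times the independence SE with two groups of 9, and 1.01 to 1.08 times with four groups of 4 or 5. Severity is moderate. What is at stake is the planned significance tests and the stated precision of the effect sizes, not the sample size or the point estimates.

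A reader might also conclude that a partially nested mixed model should replace the planned comparison at little cost. With two or three groups it would leave only about 2.5 to 7 df and widen intervals roughly 1.2 to 2.1 times, so it is at most a supplementary analysis.

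**What to change.** 1. Record each SystemCHANGE participant's session group. The article reports the trial as still recruiting, so this is one data field.
2. Keep the planned between-arm comparison, but report each effect estimate with an interval inflated by the design effect at prespecified ICCs of 0.01, 0.05 and 0.10, computed from the actual group sizes. With two groups of 9 the multipliers are 1.02, 1.09 and 1.18. State that these intervals treat the ICC as known.
3. Interpret the within-arm repeated-measures tests with the same caution, and name session-group clustering as a limitation.
4. State that the larger trial's sample size will include a design effect for group delivery.
5. If a partially nested mixed model is fitted (random group effect in the SystemCHANGE arm only, small-sample degrees of freedom), label it supplementary.

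The cost is one data field, a few sentences of analysis wording and modestly wider intervals.
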